#### **2.2.2.2 Clinical pharmacokinetics**

After oral administration, BIBF 1120 maximum plasma concentrations ( $t_{\max}$  1 to 4 h) and AUC increased dose-proportionally after single administration as well as at steady state following single daily and bidaily dosing. Steady state was reached latest within 9 days. After food intake, a trend towards an increased systemic exposure (around 20%) which was not statistically significant, and a delayed absorption was observed compared to administration of BIBF 1120 under fasted conditions. A high apparent volume of distribution during the terminal phase and a high apparent total plasma clearance for BIBF 1120 was observed. The terminal half-life varied between 7 and 19 h. The major route of elimination of total [ $^{14}\text{C}$ ] radioactivity was via biliary excretion (93.4%). The contribution of renal excretion was low (0.7%). Pharmacokinetic behavior of BIBF 1120 is similar between healthy volunteers and cancer patients, and in patients with different cancer types. As expected, there was no clinically relevant drug-drug interaction between BIBF 1120 and paclitaxel, docetaxel, carboplatin or pemetrexed at clinically used doses. All principle metabolites that were observed in humans have been found in animal studies (rats and Rhesus monkeys) after oral dosing. The principal (major) metabolites, both in humans and animals, are BIBF 1202 and its glucuronide. Plasma concentrations

needed for biological activity at VEGFR 1, 2 and 3 (compared to in vitro inhibitory concentrations) can be achieved starting with doses of 100 mg of BIBF 1120 once daily.

### **3 STUDY OBJECTIVES**

#### **3.1 Rationale for this study**

Despite recent advances into the insight of the molecular mechanism of acute myelogenous leukemia, not much improvement in the still unsatisfactory treatment of patients > 60 years has been made with standard therapy of cytarabine and anthracyclines, followed by intermediate-dose cytarabine consolidation. For patients medically unfit for this standard chemotherapy, the current standard of care consists of 5-azacytidine in patients with <30% bone marrow blasts, low-dose cytarabine in patients with non-adverse cytogenetic risk profile and >30% bone marrow blasts and best supportive care only with the addition of cytoreductive therapy, i.e. hydroxyurea, if required for leukocytosis, in patients with adverse cytogenetics and >30% bone marrow blasts. Despite different potential therapeutic options, outcome in this patient population is still dismal.

A body of data suggests that AML blasts are dependent on signal transduction pathways to mediate enhanced proliferation, apoptosis inhibition and block of differentiation. In addition, safety data suggest a good safety profile of BIBF 1120, compared to intensive standard induction therapy. For this reasons, the addition of the triple kinase inhibitor BIBF 1120 to low-dose cytarabine might improve therapy results in elderly AML patients unfit for intensive induction therapy.

##### **3.1.1 Benefit / risk ratio**

Patients eligible for this trial have a chance of survival with any other therapy of 25% after one year [2]. The risk of this trial is that addition of BIBF 1120 to low-dose cytarabine increases treatment-related death due to extensive toxicity. Since a MTD for BIBF 1120 monotherapy and for combination therapy with various cytotoxic agent has already been evaluated in clinical trials in solid tumors, it seems justified to perform an enhance dose finding for the combination therapy of BIBF 1120 and low-dose cytarabine.

The possible benefit of the trial is to decrease the rate of treatment failure in the trial population. For a single patient, this could result in increased life-span, ideally without evidence of leukemia. Given the extensively high rate of primary or secondary treatment failure in this patient population, the medical need for novel, rational therapeutic approaches for this patient population is overwhelming. As pointed out above, the molecular rationale for

the therapeutic administration of BIBF 1120 in AML is well founded. Thus, the benefit/risk ratio for a patient to participate in this trial appears favorable.

Since the application of 5-azacytidine has a proven efficacy in low-proliferating AML with  $\leq 30\%$  bone marrow blasts [17], AML patients with  $\leq 30\%$  bone marrow blasts should be treated with 5-azacytidine if possible. Accordingly, patients qualifying for an intensive treatment have a chance of achieving a complete remission of 50% and should therefore be treated with an intensive approach. However, no therapeutic approach exists in patients with  $>30\%$  bone marrow blasts and adverse cytogenetic risk unfit for an intensive treatment, and these patients have the highest need for therapy improvement. Patients with non-adverse cytogenetic risk and not qualifying for both therapy with 5-azacytidine and intensive chemotherapy only have an 18% chance of achieving a complete remission upon treatment with low-dose cytarabine alone. It therefore seems justifiable to include these patients (with AML not qualifying for both 5-azacytidine and intensive chemotherapy) into this trial.

## 3.2 Study objectives

### 3.2.1 Phase I

Primary endpoint:

- to evaluate the safety and tolerability of BIBF 1120 combined with low-dose cytarabine

### 3.2.2 Phase II

Primary endpoint:

- to evaluate the overall response rate (ORR, consisting of: CR, CRp and CRi as defined by IWG criteria) of the whole study population

Secondary endpoints:

- to compare the ORR rate of the Flt3-mutated patients versus the Flt3-wildtype patients and within different cytogenetic risk groups
- to evaluate the CR rate of the whole study population
- to compare the CR rate of the Flt3-mutated patients versus the Flt3-wildtype patients and within different cytogenetic risk groups
- to evaluate the one-year overall survival (OS) of the whole study population

---

 response criteria by the International Working Group (IWG) are defined as:

- Complete remission (CR): less than 5% bone marrow blasts and regeneration of both peripheral neutrophils to  $>1,000/\mu\text{l}$  and platelets to  $>100,000/\mu\text{l}$
- Complete remission with incomplete platelet recovery (CRp): less than 5% bone marrow blasts and regeneration of peripheral neutrophils to  $>1,000/\mu\text{l}$  with a platelet count of  $<100,000/\mu\text{l}$
- Complete remission with incomplete neutrophil recovery (CRi): less than 5% bone marrow blasts with a neutrophil count of  $<1,000/\mu\text{l}$  with or without platelet recovery

- to compare the one-year overall survival (OS) of the Flt3-mutated patients versus the Flt3-wildtype patients and within different cytogenetic risk groups
- to evaluate the relapse-free survival (RFS) of the responding patients
- to evaluate the time to response (CR, CRp or CRi) of the responding patients
- to evaluate the toxicity in the whole study population
- to evaluate the development of biomarkers indicating the course of disease, including genetic, epigenetic, transcriptional, protein and phosphoprotein markers in leukemic blasts, bone marrow, peripheral blood cells, serum and plasma, and bone marrow microvessel density.

### 3.3 Study design

This is a single-arm, prospective, multi-center phase I/II study. Patients 60 years or older with relapsed or refractory (phase I only) or newly diagnosed AML medically unfit for or unwilling to receive an intensive standard chemotherapy will receive intermittent low-dose cytarabine s.c. combined with a continuous treatment with BIBF 1120. Dose escalation in the phase I part will be a classical 3 + 3 design with an increased starting dose level due to the experiences of the MTD determination in monotherapy studies. For further details see chapter 5.

## 4 SELECTION, REGISTRATION AND WITHDRAWAL OF PATIENTS

### 4.1 Number of patients

According to the power calculations given in 8.1,  $n = 122 + X$  patients will be included in the phase II of the study.

### 4.2 Admission criteria

#### 4.2.1 Inclusion criteria

- Patients with newly diagnosed (Phase I and II) AML (except APL) according to the FAB or WHO classification, including AML evolving from MDS or other hematological diseases and AML after previous cytotoxic therapy or radiation (secondary AML), not eligible for a standard induction and consolidation therapy.
- Phase I only: Patients with relapsed or refractory AML (except APL) according to the FAB or WHO classification, not eligible for an intensive salvage chemotherapy or an allogeneic stem cell transplantation

- Bone marrow aspirate or biopsy must contain > 20% blasts of all nucleated cells. In AML FAB M6  $\geq$  30% of non-erythroid cells in the bone marrow must be leukemic blasts. In patients with 20-30% blasts, the indication for a treatment with hypomethylating agents (5-azacitidine or decitabine) should be considered prior to inclusion into the trial.
- Age  $\geq$  60 years
- Informed consent, personally signed and dated to participate in the study
- Male patients enrolled in this trial must use adequate barrier birth control measures during the course of treatment and for at least 3 months after the last administration of study therapy (low-dose cytarabine and/or BIBF 1120).
- Patients at risk for hollow organ perforation (i.e., ulcerative colitis, Crohn's disease, sigma diverticulitis) should only be included if the potential benefit of the study participation outweighs the risk for perforation in the opinion of the investigator.

#### 4.2.2 Exclusion criteria

- Patients with 20-30% bone marrow blasts which are qualifying for and consenting into a therapy with hypomethylating agents
- Known central nervous system manifestation of AML
- Inadequate liver function (ALT and AST  $\geq$  2.5 x ULN) if not caused by leukemic infiltration
- Known chronically active hepatitis C infection or acute hepatitis
- Chronically impaired renal function (creatinin clearance < 30 ml/min)
- Uncontrolled hypertension with a resting pressure systolic > 160 mmHg or diastolic > 95 mmHg despite adequate treatment
- severe trauma or surgery within 4 weeks of study entry
- severe, non-healing wounds, ulcer or fracture
- Uncontrolled active infection
- Concurrent malignancies other than AML or other severe diseases which in the opinion of the investigator are likely to influence the endpoint assessment
- Hypersensitivity to cytarabine (not including drug fever or exanthema)
- Phase II only: Previous treatment of AML except hydroxyurea up to 24 hours before study medication
- Phase II only: Previous therapy with tyrosine kinase inhibitors or angiogenesis inhibitors
- Parallel participation in another clinical trial for the same indication. Eligibility of patients with investigational drug therapy outside of this trial during or within 4 weeks of study entry should be discussed with the study office prior to study entry
- Any severe concomitant condition, which makes it undesirable for the patient to participate in the study or which could jeopardize compliance with the protocol

## 4.3 Patient registration

### 4.3.1 Registration

Registration will be performed by the Department of Medicine A in Muenster during regular office hours (Monday through Friday 8 am to 5 pm) either by [contact] or per [contact].

#### **Details for registration are:**

- sex and date of birth
- Diagnosis (according to the FAB-classification)
- Study centre and name of the physician
- All inclusion criteria fulfilled
- no Exclusion criteria

During the registration process, a patient registration number will be assigned to the patient by the Study Office with the following format:

**ZZZ – NNN**

ZZZ = three numbers for the Center

NNN = Unique patient identification number (continuously increasing number)

## 4.4 Withdrawal of patients

A patient is free to withdraw from the study at any time for any reason without prejudice to his/her future medical care by the physician or at the institution. The Investigator may also withdraw the patient at any time in the interest of patient safety. The primary reason for withdrawal must be recorded in the patient's medical record and on the withdrawal form in the Case Report Form (CRF).

## **5 STUDY, STANDARD AND CONCOMITANT TREATMENTS**

### **5.1 Investigational product BIBF1120**

BIBF 1120 is a small molecule receptor tyrosine kinase (RTK) inhibitor, with competitive inhibition of ATP-binding to the ATP-binding site. In dosages above 100 mg once daily, it inhibits the activity of the RTK VEGFR 1-3, FGFR1, FGFR3, PDGFR $\alpha$  and PDGFR $\beta$ . For full details of the pre-clinical and clinical information please refer to the summary of product characteristics and the investigators brochure.

#### **5.1.1 Relevant physical, chemical and pharmaceutical properties**

BIBF 1120 is a yellow, highly crystalline, hemihydrous powder with a high water solubility. BIBF 1120 is provided as soft gelatin capsules containing a suspension of milled active as the salt. It is available in dose strengths corresponding to 100 mg (peach, oblong capsules) and 150 mg (brown, oblong capsules) and is packaged in bottles containing 30 capsules.

#### **5.1.2 Instructions for storage and handling**

In the solid state BIBF 1120 is stable with a shelf life of 36 months. The capsules are packaged in bottles and have to be stored below 30°C. BIBF 1120 will be swallowed unchewed after a meal every 12 hours ( $\pm$  1 hour), i.e. daily at about the same time in the morning and in the evening.

#### **5.1.3 Interactions with concomitant medications**

In vitro data showed that BIBF 1120 has no potential for drug-drug interactions via CYP-450-enzymes.

### **5.2 Cytarabine (AraC)**

The low-dose cytarabine treatment used in this protocol is approved and belongs to the standard of care of the population included in this study.

Cytarabine belongs to a group of chemotherapeutic agents called antimetabolites. Although the mechanism of action is not completely understood, it appears that cytarabine acts through the inhibition of DNA polymerase. A limited, but significant, incorporation of cytarabine into both DNA and RNA has also been reported.

Cytarabine is not active orally. It may be given by intravenous infusion or injection, subcutaneously, or into the liquor space. When large intravenous doses are given quickly,

patients are frequently nauseated and may vomit for several hours after injection. This problem tends to be less severe when the drug is infused.

A cytarabine syndrome has been reported to occur in patients who received cytarabine. It is characterized by fever, myalgia, bone pain, occasionally chest pain, maculopapular rash, conjunctivitis and malaise. It usually occurs 6-12 hours following drug administration. Corticosteroids have been shown to be beneficial in treating or preventing this syndrome. If the symptoms of the syndrome are deemed treatable, corticosteroids should be contemplated as well as continuation of therapy with cytarabine.

Like other cytotoxic drugs, cytarabine may induce anemia, leukopenia, thrombocytopenia and hyperuricemia secondary to rapid lysis of neoplastic cells.

Rarely, severe skin rash, leading to desquamation has been reported.

For full details of the drug information please refer to the “Fachinformationsverzeichnis Deutschland” in its latest version.

### 5.3 Drug accountability

The drug BIBF1120 will be distributed to the responsible investigator in the center in bottles containing the drug supply sufficient for two therapy cycles (4 x 30 capsules for dose levels 1 [100 mg bidaily] and 2 [150 mg bidaily], 8 x 30 capsules for dose level 3 [200 mg bidaily]). Should a daily dose of 2 x 200 mg be evaluated as the recommended dose, an additional vial of 150 mg capsules (30 capsules) will also distributed to the centers by the initial drug distribution to cover dose reductions. For each dose level within the phase I part and for the phase II part, each center will be supplied with an initial delivery of study medication sufficient for two cycles.

**The center is responsible for ordering more supply at least three working days ahead of time.**

AraC will be ordered from the local pharmacy by the study center and distributed to the patient according to local standard ordering procedures.

Each center has to document in a list, when which drug was given to whom. This list has to contain the date, the patients number, the batch number, the use-by date and the number of capsules / amount of AraC dispensed.

The patient or the person applying the drug has to document the drug application and - in case of a failure to take the medication - a short statement, why medication was not taken, in a

standardized diary provided by the study center. Leftover study medication will be collected by the study center upon regular visits.

## 5.4 Study treatment overview

### 5.4.1 Treatment and observation

Patients will receive low-dose cytarabine in a dose of 20 mg as subcutaneous injection twice daily on days 1-10 of each cycle and BIBF 1120 twice daily (for dose level, see below) as an oral dose throughout the cycle on a 28-day cycle. A bone marrow aspirate and a complete blood count (CBC) with differential blood count for response evaluation will be performed between days 24 and 28 of each cycle. Patients will receive additional cycles from day 29 on for up to six cycles in total if the following applies: I. absence of significant disease progression as judged by the investigator, II. absence of unacceptable toxicity, and III. no adequate response (CR, CRp or CRi) in the bone marrow evaluation between days 24 and 28. The application of the next therapy cycle can be postponed for up to 28 days (up to day 57) due to the following reasons: A) the application of cytarabine on day 29 is undesirable in the opinion of the investigator, B) I. and II. applies and the result of the response assessment is pending when the next cycle is due, or C) I. and II. applies and the response assessment could not be performed\* (i.e., reduced general condition, infectious complications) or was not evaluable\* (i.e., no aspirated bone marrow spicules). Under these circumstances, patients will be bridged to the next cycle with BIBF 1120 at the last dosage of the previous cycle. In case of the achievement of a CR, CRp or CRi, or in case of no evaluable response by day 57, patients switch to observation. In case of progressive disease (for definition of leukemia progression see the asterisk on the following page) or intolerable toxicity, patients will be observed for survival (see 5.4.2 and 5.4.3).

- \* In these cases, bone marrow aspiration will be postponed / repeated together with physical examination, vital signs and body weight (see 6.2, table 2 for details). These bone marrow results have to be available by day 57 at latest. A core biopsy is recommended in a repeat bone marrow biopsy in case of an initial dry tap.

## Treatment Plan:

[figure not shown]

## Treatment overview:

[figure not shown]

a Clinically meaningful disease progression as assessed by the investigator. Assessment takes into account, but is not restricted to: blast count in bone marrow and peripheral blood, tumor lysis parameters, extramedullary manifestations, and worsening of clinical or laboratory parameters or general condition attributable to leukemia progression.

b In phase I, patients will be followed up only until 28 days after the last administration of study medication.

### 5.4.2 Phase I – part

The optimum dosage of BIBF 1120 in combination with low-dose cytarabine will be determined in a phase I part. Based on acceptable safety data for BIBF 1120 monotherapy, there will be a rapid dose finding. Dose finding will proceed in a classical 3+3-design. Predefined dose levels are: 100mg (dose level 1), 150mg, (dose level 2), and 200mg (dose level 3) twice daily. A cohort of three patients will be treated in each dose level and toxicity will be assessed in the first treatment cycle (28 days) by Common Terminology Criteria for Adverse Events V 4.0 (CTCAE). Patients evaluable for this safety analysis have to have received at least one dose of BIBF1120 and AraC. In case of no dose limiting toxicity (DLT), the dose will be increased by one dose level. In case of one DLT, up to three further patients will be recruited into the same dose level. If >1 DLT occurs in one dose level in up to six patients, this dose level will not be further evaluated. The highest dose level with  $\leq 1$  DLT out of six patients will be defined as the maximum tolerable dose (MTD) and will be evaluated in the phase II part of the study after approval of the data monitoring committee (DMC). Dose levels considered for phase II with less than six patients evaluated (i.e. no DLT in three patients) will further recruit patients until a total of six evaluable patients and will be chosen for phase II only if the aforementioned condition ( $\leq 1$  DLT out of six patients) applies. In case of >1 DLT in the dose level 1 cohort, the dose will be decreased to dose level 0 (100 mg BIBF 1120 once daily). The study will not proceed to the phase II part if >1 DLT occurs in dose level 0. A DLT is defined as every severe adverse reaction CTC grade IV with possible or definite relationship to the study drug BIBF1120. Therapy-related cytopenias as signs of an intended antileukemic activity do not fulfill the definition of an adverse events and therefore cannot constitute an SAE or DLT. The following known, frequent and often inevitable complications from therapy-related cytopenias are also excluded from DLT: neutropenic fever, neutropenic infections and thrombocytopenic bleedings. Notwithstanding, these complications may constitute a DLT if occurring in an unexpected high frequency, as judged by the DMC, and should be reported as an AE or SAE as appropriate (see 7). Complications attributable to disease progression in the judgement of the investigator are also excluded from DLT. These include:

- neutropenic infections due to disease progression\*
- thrombocytopenic bleedings due to disease progression\*
- deterioration of the general condition due to leukemia progression\*
- laboratory abnormalities due to leukemia progression\*
- death due to disease progression\*

- tumor lysis syndrome due to disease progression\*
- organ failure (i.e. renal insufficiency, coagulopathy, respiratory failure, hypotension) due to disease progression\*

\*leukemia progression defined as at least one of the following: reappearance of blasts in the peripheral blood, raising blast counts in the peripheral blood, raising blast counts in bone marrow, appearance, reappearance or progression of chloromas, raising lactate dehydrogenase serum level with no other explanation)

Patients responding after the therapy (CR, CRp, CRi) or with progressive disease or intolerable toxicity will be observed until 28 days after the last application of study medication. Patients with a partial remission or stable disease will continue in protocol treatment for up to six therapy cycles.

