#### 5.4.4.2 Dose modifications for hematological toxicity of BIBF1120 and cytarabine.

For an effective antileukemic activity, a hematotoxicity is an unavoidable side effect of the combination therapy. Since only patients with persisting leukemia receive additional

chemotherapy / BIBF cycles, no routine dose modifications or dose delays are considered for hematological toxicity during the combination therapy. In case of grade 3 or 4 complications of hematotoxicity (thrombocytopenic bleeding, neutropenic infections, neutropenic fever) both cytarabine and BIBF1120 will be paused and will both be restarted without dose reduction upon improvement to grade 2 or lower. If, however, a continuation of the combination treatment places the patient to an inadequate risk in the opinion of the investigator, study treatment including treatment with cytarabine should be discontinued.

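### A single dose of each drug makes a phase I patient evaluable for a 28-day DLT window, so patients lost early for reasons unrelated to BIBF 1120 normally count as free of DLT and tilt the MTD upward

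*Protocol*

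**What the plan says.** Protocol section 5.4.2 sets the DLT window as one cycle: "toxicity will be assessed in the first treatment cycle (28 days". The next sentence defines who counts: "Patients evaluable for this safety analysis have to have received at least one dose of BIBF1120 and AraC".

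The counting rules follow. Each level starts with three patients, and a clean cohort moves the trial up: "In case of no dose limiting toxicity (DLT), the dose will be increased by one dose level". A single event instead enlarges the cohort to as many as six. A second event closes the level: "If >1 DLT occurs in one dose level in up to six patients, this dose level will not be further evaluated". A level goes forward to phase II only with six evaluable patients and no more than one DLT among them.

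A DLT must be grade IV and possibly or definitely related to BIBF 1120. Complications that the investigator attributes to progression, death included, are not DLTs. Section 4.4 lets patients withdraw at any time. No section adds a minimum number of doses, a minimum observation time or a rule for replacing phase I patients.

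Planned treatment in the window (section 5.4.1) is cytarabine "on days 1-10 of each cycle and BIBF 1120 twice daily", the latter continuing through the cycle.

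**The concern.** A 3+3 design reads each place without a DLT as evidence that the dose was tolerated for the whole window. Here a place can be filled by a patient with a small part of the planned exposure, or one whose observation ended after days.

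Short exposure says little about this drug. Section 2.2.2 puts steady state at up to 9 days, and says the known liver enzyme elevations usually appeared within the first two months. Phase I also admits relapsed or refractory patients aged 60 or over who are unfit for intensive salvage (section 4.2.1), so some early loss is foreseeable.

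At stake is the dose carried into a phase II part of 122 patients. With three to six patients per level, one uninformative place can change a decision. Because escalation uses the rule in real time, a later analysis plan cannot repair it.

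**Working it through.** The protocol gives no operating characteristic, target DLT rate or loss rate for phase I, so there is no stated figure to reproduce.

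**Inputs.** The window, schedule and counting rules come from sections 5.4.1 and 5.4.2. Two quantities are assumptions: *p*, the true DLT risk with full exposure and observation, and *d*, the share of patients lost early for reasons unrelated to BIBF 1120.

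**1. Exposure behind one place.** At the twice-daily levels the window holds 2 × 28 = 56 BIBF 1120 doses and 2 × 10 = 20 cytarabine injections. A patient leaving at the end of week 1 has had 14/20 = 70% of the cytarabine but 14/56 = 25% of the BIBF 1120. The evaluability rule would accept 1 of 56.

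**2. One such patient in a cohort.** P(0 DLT in 3) = (1−p)³, and becomes (1−p)² if one of the three cannot show a DLT.
- p = 0.33: 0.301 becomes 0.449.
- p = 0.50: 0.125 becomes 0.250.

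P(≤1 DLT in 6) = (1−p)⁶ + 6p(1−p)⁵. With one such patient among the six, n falls to 5. At p = 0.33, 0.358 becomes 0.468.

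**3. Random loss.** If those lost have no DLT, the per-patient risk falls to p′ = p(1−d). For p = 0.33:

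| d | p′ | P(≤1 of 6) |
|---|---|---|
| 0 | 0.330 | 0.358 |
| 10% | 0.297 | 0.427 |
| 20% | 0.264 | 0.501 |
| 30% | 0.231 | 0.580 |

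For p = 0.40 the values at 0, 10% and 20% are 0.233, 0.301 and 0.378.

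**4. Whole escalation rule.** Passing at one level is not the same as being chosen. Enumerating the full rule over levels 0 to 3, starting at level 1, gives these probabilities that level 3 becomes the MTD:

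| Assumed true DLT rates, levels 0/1/2/3 | d = 0 | d = 10% | d = 20% |
|---|---|---|---|
| 0.05 / 0.10 / 0.25 / 0.40 | 0.127 | 0.181 | 0.251 |
| 0.05 / 0.15 / 0.33 / 0.50 | 0.039 | 0.069 | 0.116 |
| 0.10 / 0.25 / 0.40 / 0.50 | 0.020 | 0.040 | 0.075 |

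The choice shifts upward in every scenario tried.

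**5. A rough anchor for d.** The only mortality figure is the 25% one-year survival in section 3.1.1. Under an assumed constant hazard, deaths by day 7 are 1 − 0.25^(7/365) = 2.6%, and by day 28 they are 1 − 0.25^(28/365) = 10%. At p = 0.33, P(≤1 of 6) is then about 0.375 or 0.427. Early hazard and mortality in relapsed or refractory disease may be higher, and withdrawals add to the loss.

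**The case against.** Several points weigh on the other side, and most of them stand as limits on size.

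- **Stopping the drug does not end observation.** The treatment overview footnote in 5.4.1, and sections 5.4.2 and 7.2, keep patients under observation for adverse events until 28 days after the last dose. Someone stopping on day 5 is followed to about day 33. For such a patient the gap is missing exposure. Only death or a withdrawal that ends observation cuts follow-up short.
- **A pause is not a loss.** A reader might infer that a patient whose drugs are held for a neutropenic infection counts as an early leaver, since section 5.4.4.2 says "both cytarabine and BIBF1120 will be paused". The same sentence has both drugs restarted on improvement, so a pause alone does not support the point.
- **A non-DLT score is not inevitable.** A reader might infer that these patients can never be scored otherwise. Section 5.4.2 lets the data monitoring committee (DMC) treat cytopenic complications as DLTs if unexpectedly frequent, and any other related grade IV event still counts.
- **Committee review.** The DMC sees a report after each dose level and approves the phase II dose (sections 5.4.2 and 9.1). This is a real safeguard, but nothing shown tells the committee to set aside or replace an under-exposed patient. Its charter, Attachment K, is not shown.
- **The sentence is worded as a minimum.** It could be read as necessary but not sufficient. It is nevertheless the only criterion given, so it works as the definition.
- **The larger figures are not predictions.** Nothing in the protocol supports 20% or 30% as the expected loss.

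**Conclusion.** The gap is real and moderate. Followed as written, the protocol lets patients who were barely exposed or only briefly observed occupy 3+3 places as non-DLTs, and this favours a higher MTD. The direction needs only that patients lost early contribute few or no DLTs.

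The size is uncertain. At p = 0.33, the chance of at most one DLT in six moves from 0.358 to about 0.43 at 10% loss, 0.50 at 20% and 0.58 at 30%. For a given loss rate these are upper bounds, since those lost are given zero DLT risk despite partial exposure and, often, continued follow-up. They also assume that leaving is unrelated to a patient's susceptibility to DLT. The documents do not support a claim that the selected dose will be too toxic.

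**What to change.** In section 5.4.2, separate the DLT-evaluable set from the general safety set.

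- **DLT-evaluable:** the patient had a DLT, or completed the 28-day observation with a prespecified minimum share of the planned BIBF 1120 doses. The sponsor sets the share.
- **Exception:** patients whose dosing was interrupted or stopped for BIBF 1120-related toxicity stay evaluable and are not replaced. A bare minimum-dose rule would drop patients interrupted for related grade 3 toxicity, which is not a DLT and may mean a delay of up to 30 days (section 5.4.4.3). That would discard tolerability information and make the denominator depend on the drug's own effect.
- **Replacement:** only patients who leave early without a DLT for reasons unrelated to BIBF 1120.
- **Safety tables:** keep the one-dose set for these.

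The cost is a wording change, an occasional replacement patient and some weeks added to phase I. Replacement brings the risk back to the d = 0 row only if leaving is unrelated to DLT susceptibility, so the reason for each early exit should be recorded and shown to the DMC.
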